## **7 Study Governance**

### **7.1 Ethical Conduct of the study**

The trial will be conducted in compliance with the principles of the Declaration of Helsinki (1996), the principles of Good Clinical Practice (GCP) and in accordance with all applicable regulatory requirements including but not limited to the Research Governance Framework and the Medicines for Human Use (Clinical Trial) Regulations 2004, as amended in 2006 and any subsequent amendments. This protocol and related documents will be submitted for review to the Research Ethics Committee (REC), and to the Medicines and Healthcare products Regulatory Agency (MHRA) for Clinical Trial Authorisation. The Chief Investigator will submit a final report at conclusion of the trial to the KHP-CTO (on behalf of the Sponsor), the REC and the MHRA within the timelines defined in the Regulations. A favourable ethical opinion will be obtained from the appropriate REC, MHRA and local R&D approval will be obtained prior to commencement of the study. Written informed consent will be obtained and documented in the participants hand-held notes. A sticker will also be placed on the participant's notes.

### **7.2 Investigator responsibilities**

The Investigator is responsible for the overall conduct of the study at the site and compliance with the protocol and any protocol amendments. In accordance with the principles of GCP, the following areas listed in this section are also the responsibility of the Investigator. Responsibilities may be delegated to an appropriate member of study site staff. Delegated tasks must be documented on a Delegation Log and signed by all those named on the list.

### **7.3 Informed Consent**

The Investigator is responsible for ensuring informed consent is obtained before any protocol specific procedures are carried out. The decision of a participant to participate in clinical research is voluntary and should be based on a clear understanding of what is involved. Participants must receive adequate oral and written information – appropriate Participant Information and Informed Consent Forms will be provided. The oral explanation to the participant should be performed by an Investigator, and must cover all the elements specified in the Participant Information Sheet/Informed Consent. The participant must be given every opportunity to clarify any points they do not understand and, if necessary, ask for more information. The participant must be given sufficient time to consider the information provided. It should be emphasised that the participant may withdraw their consent to participate at any time without loss of benefits to which they otherwise would be entitled. The participant should be informed and agree to their medical records being inspected by regulatory authorities but understand that their name will not be disclosed outside the hospital. The Investigator or delegated member of the trial team and the participant should sign and date the Informed Consent

[figure not shown]

Form(s) to confirm that consent has been obtained. The participant should receive a copy of this document and a copy filed in the Investigator Site File (ISF).

#### **7.4 Study Site Staff**

The Principal Investigator and site staff must be familiar with the protocol and the study requirements. It is the Investigator's responsibility to ensure that all staff assisting with the study are adequately informed about the protocol and their trial related duties and be GCP trained.

#### **7.5 Data Recording**

The Investigator is responsible for the quality of the data recorded in the electronic clinical research files.

#### **7.6 Data sharing and preservation strategy**

The Investigators will comply with the Kings College London (KCL) principles on data sharing and preservation. The consent form states that other researchers may wish to access (anonymised) data in future. The trial statistician will (in collaboration with the CI) manage access rights to the data set. Prospective new users must demonstrate compliance with legal, data protection and ethical guidelines before any data are released. We anticipate that anonymised SUPPORT data will be shared with other researchers to enable international prospective on prediction of preterm birth. The Co-sponsors or their delegates will ensure all other documents required by GCP are retained in a research Master File.

#### **7.7 GCP Training**

All study staff must hold evidence of appropriate GCP training or undergo GCP training. This should be updated every two years throughout the trial.

#### **7.8 Confidentiality**

All laboratory specimens, evaluation forms, reports, and other records must be identified in a manner designed to maintain participant confidentiality. All records must be kept in a secure storage area with limited access. Clinical information will not be released without the written permission of the participant, except as necessary for monitoring and auditing by the Co-Sponsors, their designee, Regulatory Authorities, or the REC. The Investigator and study site staff involved with this study may not disclose or use for any purpose other than performance of the study, any data, record, or other unpublished, confidential information disclosed to those individuals for the purpose of the study. Prior written agreement from the Co-Sponsors or their designee must be obtained for the disclosure of any said confidential information to other parties.

#### **7.9 Data Protection**

All Investigators and study site staff must comply with the requirements of the Data Protection Act 1998 with regard to the collection, storage, processing and disclosure of personal information and will uphold the Act's core principles. Computers used to collate the data will have limited access measures via user names and passwords. Published results will not contain any personal data that could allow identification of individual participants

#### **7.10 Study sponsor**

Kings College London/Guys and St Thomas' NHS Foundation trust are co-sponsors of the study.

[figure not shown]

### **7.11 NHS Trust Research and Development (R&D)**

Individual sites will only start recruitment once they have received approval from their NHS Trust Research and Development (R&D) office. Applications to R&D offices will be submitted through the NIHR Co-ordinated System for gaining NHS permission

### **7.12 Study Coordinating Centre**

The trial coordinating centre will be Division of Women's Health, Kings College London, where the study coordinator will be based. The Division of Women's Health will be responsible for study data entry, statistical analysis, servicing both the Data Monitoring Committee (DMC) and the Trial Steering Committee (TSC) and, in collaboration with the Chief Investigator and Local Research Midwives/Nurses, for the day to day running of the study including recruitment of sites and training of staff.

### **7.13 Trial Steering Committee (TSC)**

The role of the TSC is to provide the overall supervision of the study. The TSC should monitor the progress of the study and conduct and advise on its scientific credibility. The TSC will consider and act, as appropriate, upon the recommendations of the DMC and ultimately carries the responsibility for deciding whether the trial needs to be stopped on the grounds of safety or efficacy. The TSC will consist of an independent chair and at least two other independent members (not involved in study recruitment and not employed by any organisation directly involved in study conduct. A representative(s) from the Preterm Birth Patient Public Involvement group will be included. The first meeting will take place 1 month after trial start date; frequency will be decided at the first meeting.

### **7.14 Data Monitoring Committee (DMC)**

A DMC independent of the applicants and TSC will review the progress of the trial at least annually and provide advice on the conduct of the trial to the TSC. The committee will periodically review study progress and outcomes. The timings and content of the DMC reviews will be detailed in a DMC charter which will be agreed at its first meeting. The DMC will meet 3 months after the trial start date; frequency of meeting will be decided at the first meeting.

## **8 Safety**

### **8.1 Assessment of Safety**

This trial is deemed by the Sponsor to be a Type A trial as the IMP is used routinely with no higher risk to the patient than standard medical care.

The data monitoring committee will be established to ensure the wellbeing of study participants. The committee will periodically review study progress and outcomes as well as reports of serious adverse events (SAEs). The DMC will, if appropriate, make recommendations regarding the continuance of the study or modification of the study protocol.

### **8.2 Procedures for Recording and Reporting Adverse Events**

#### **8.2.1 Serious adverse Event (SAE), Serious Adverse Reaction (SAR)**

The Medicines for Human Use (Clinical Trials) Regulations 2004 and Amended Regulations 2006 gives the following definitions:

**Adverse Event (AE):** Any untoward medical occurrence in a subject to whom a medicinal product has been administered including occurrences which are not necessarily caused by or related to that product.

[figure not shown]

**Adverse Reaction (AR):** Any untoward and unintended response in a subject to an investigational medicinal product which is related to any dose administered to that subject.

**Unexpected Adverse Reaction (UAR):** An adverse reaction the nature and severity of which is not consistent with the information about the medicinal product in question set out in the Investigator's Brochure (IB) relating to the trial in question (for any other investigational product)

**Serious adverse Event (SAE), Serious Adverse Reaction (SAR) or Unexpected Serious Adverse Reaction (SUSAR):**

Any adverse event, adverse reaction or unexpected adverse reaction, respectively, that

- Results in death
- Is life-threatening;
- Required hospitalisation or prolongation of existing hospitalisation;
- Results in persistent or significant disability or incapacity - Consists of a congenital anomaly or birth defect.
- Is otherwise considered medically significant by the investigator.

All AEs and SAEs must be recorded from the time a participant is randomized to treatment until 30 days after stopping taking study drug and until pregnancy outcome (28 days after delivery). The Investigator should ask about the occurrence of AEs/SAEs at every visit during the study. Open-ended and non-leading verbal questioning of the participant should be used to enquire about AE/SAE occurrence. Participants should also be asked if they have been admitted to hospital, had any accidents, used any new medicines or changed concomitant medication regimens. If there is any doubt as to whether a clinical observation is an AE/SAE, the event should be recorded. Hospitalisations for treatment planned prior to randomisation and hospitalisation for elective treatment of a pre-existing condition will not be considered as an SAE. Complications occurring during such hospitalisation will be AE/SAEs.

**Important Medical Events (IME):** Events that may not be immediately life-threatening or result in death or hospitalisation but may jeopardise the patient or may require intervention to prevent one of the other outcomes listed in the definition above should also be considered serious.

### 8.2.2 Adverse events which do not require reporting

Expected SAEs are those events which are expected in the patient population or as a result of the routine care/treatment of a patient. The interventions they will be receiving are those which would be offered routinely in clinical practice. Cervical cerclage insertion is an established surgical procedure, which is associated with minimal risks. These include infection, miscarriage, bleeding, difficulty with suture removal and preterm prelabour rupture of membranes. The cervical pessary is not associated with known risk. Progesterone pessaries have risk of allergy. Symptoms of overdose may include somnolence, dizziness, euphoria or dysmenorrhoea (latter not applicable for pregnant women). Treatment is observation and, if necessary, symptomatic and supportive measures should be provided.

Serious adverse events/reactions which are unrelated to these clinical procedures will be reported as SAEs.

Events that are primary or secondary outcome measures are not considered to be SAEs and will be reported in the normal way, on the appropriate electronic case report form.

Maternal:

- Premature labour
- Premature rupture of membranes
- Chorioamnionitis

Infant:

[figure not shown]

- Perinatal death (unless unexpected in this population)
- Low birth weight
- Requirement for supplemental oxygen or ventilation support
- Complications of prematurity (eg IVH, NEC, encephalopathy, seizures, hypoglycaemia) unless unexpected in this population ☐ Admission of the baby to the neonatal unit

In addition the following common pregnancy complication events will not be considered SAEs: hospitalisation for pre-eclampsia or pregnancy induced hypertension, hospitalisation for symptoms of preterm labour (e.g. rupture of membranes, vaginal bleeding); hospitalisation for maternal discomfort; hospitalisation for rest; hospitalisation for observation or monitoring for which the woman is admitted for a period of less than 12 h; delivery complications such as caesarean section or postpartum haemorrhage.

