### 1.3 Rationale for study

There have been no direct comparison of all three of these interventions and as such, there are no guidelines as to the optimal management of high-risk women who develop a sonographic short cervix. Women at high risk of sPTB who develop a short cervix cannot, at present, be counselled about which is the most suitable intervention to reduce their risk of delivering prematurely. Currently, cervical cerclage is the Royal College of Obstetricians (RCOG) recommended treatment for women with a short cervix <25mm and a history of 1 or more late miscarriages or preterm birth.

Our research group recently published an exploratory observational study to evaluate the relationship between proinflammatory cytokines, cervical shortening and intervention, within which 37 women who developed a short cervix were randomised to treatment with vaginal progesterone ( $n=17$ ) or cervical cerclage ( $n=19$ ). A clinically important trend towards benefit (gestation at delivery) was noted in the cerclage group [mean gestation 33.7 weeks' cerclage versus 31.5 weeks' progesterone] although this result did not achieve statistical significance.

Alfirevic *et al* compared retrospectively three separate cohorts of women with previous sPTB <34 weeks and short cervix treated with cerclage ( $n=142$ ), vaginal progesterone ( $n=59$ ) or a pessary ( $n=42$ ). There were no significant differences in rates of perinatal loss, neonatal morbidity or sPTB, apart from a higher rate of sPTB before 34 weeks' gestation in the vaginal progesterone vs pessary groups. It was concluded that randomized comparisons of these three management strategies, or combinations thereof, are needed to determine the optimal management of these women. If a randomised study, such as the one proposed, showed that the three treatments were equally efficacious, then women and clinicians would have greater choice regarding treatment plans, expensive surgery (and potential complications) could be avoided. The pessary could be inserted at a later gestational age, when cerclage is no longer performed, potentially in an outpatient setting.

This randomised controlled trial will answer the current clinical dilemma of which is the most effective method to treat women at high risk of sPTB who develop a short cervix.

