### 8.2.3 Reporting Responsibilities

All SAEs, SARs and SUSARs (excepting those specified in this protocol as not requiring reporting) will be reported immediately (and certainly no later than 24hrs) by the Investigator to the KHP-CTO and CI for review in accordance with the current Pharmacovigilance Policy. The KHP-CTO will report SUSARs to the regulatory authorities (MHRA, competent authorities of other EEA (European Economic Area) states in which the trial is taking place. The Chief Investigator will report to the relevant ethics committee. Reporting timelines are as follows:

- ☐ SUSARs which are fatal or life-threatening must be reported not later than 7 days after the sponsor is first aware of the reaction. Any additional relevant information must be reported within a further 8 days.
- ☐ SUSARs that are not fatal or life-threatening must be reported within 15 days of the sponsor first becoming
- ☐ aware of the reaction.

The Chief Investigator and KHP-CTO (on behalf of the co-sponsors), will submit a Development Safety Update Report (DSUR) relating to this trial IMP, to the MHRA and REC annually.

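### Section 8.2.2 as worded leaves treatment-related serious events out of SAE reporting, conflicts with section 8.2.3, and names expected risks unequally across the three arms

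*Protocol*

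**What the plan says.** Protocol section 8.2.2 lists what need not be reported. It opens with a definition: "Expected SAEs are those events which are expected in the patient population or as a result of the routine care/treatment of a patient".

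It then goes through the treatments. For cerclage: "These include infection, miscarriage, bleeding, difficulty with suture removal and preterm prelabour rupture of membranes". For the device: "The cervical pessary is not associated with known risk". For progesterone it names allergy and some symptoms of overdose. The reporting sentence follows: "Serious adverse events/reactions which are unrelated to these clinical procedures will be reported as SAEs".

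The same section adds two exemptions that apply to every arm. Events that are trial outcomes go to the case report form; the maternal examples are preterm labour, membrane rupture and chorioamnionitis. Certain common pregnancy events are not SAEs, among them admission for bleeding or membrane rupture as a symptom of preterm labour.

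Section 8.2.3 sets the expedited rule: "All SAEs, SARs and SUSARs (excepting those specified in this protocol as not requiring reporting) will be reported immediately", with 24 hours as the limit. Section 8.2.1 requires every AE and SAE to be recorded from randomisation onwards. Section 8.1 has the DMC look at progress, outcomes and SAE reports, and section 7.14 leaves the content of its reviews to a charter.

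**The concern.** Safety reporting exists first of all to pick up serious events that the treatment may have caused. The sentence in 8.2.2 points the other way: it sends unrelated serious events to SAE reporting and is silent on related ones, in a section about what need not be reported.

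The second difficulty is comparability. The trial sets surgery, a device and a drug side by side as an equivalence study (section 5). If efficacy proves similar, harms weigh heavily in the choice, and section 1.3 names as a benefit that "expensive surgery (and potential complications) could be avoided". If a serious event is expected, and so exempt, in one arm but reportable in another, a difference in reported SAE counts may reflect the rule and not the treatments.

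**Working it through.** The protocol states no SAE rate, so there is no figure to reproduce. The check sets the sections side by side.

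**1. The sentence taken literally.** Unrelated serious events are reported as SAEs. Related ones are not mentioned, and the opening definition counts events resulting from treatment as expected. On the wording, related serious events in all three arms are left out.

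**2. Whether 8.2.3 repairs this.** It requires SARs. Section 8.2.1 defines an adverse reaction as a response related to the investigational product, and the synopsis and section 3.4 list all three treatments under that label, so a SAR is related by definition. But 8.2.3 excepts events that the protocol exempts elsewhere, which brings 8.2.2 back in. One section asks for related serious events, the other leaves them out, and the exception clause does not say which prevails.

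**3. Which cerclage risks are exempt only for cerclage.**

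| Risk named for cerclage | Exempt in every arm anyway? | Left as a possible arm difference |
|---|---|---|
| Membrane rupture | Yes, as an outcome event | None |
| Infection | Chorioamnionitis only | Other infection |
| Bleeding | Admission for bleeding as a preterm-labour symptom; postpartum haemorrhage | Procedural bleeding |
| Miscarriage | Unclear; may count as an outcome (fetal mortality, section 2.4.2 vi) | Possibly |
| Suture-removal difficulty | No | No like-for-like event in women without a suture |

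Of the five named risks, two or three can give a like-for-like difference: other infection, procedural bleeding and possibly miscarriage.

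**4. Direction.** For those events, take equal true rates in the cerclage and pessary arms, and let s_c and s_p be the shares left unreported. With 1:1:1 allocation, the expected ratio of reported counts is

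reported cerclage / reported pessary = (1 − s_c) / (1 − s_p).

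- If related events are exempt in every arm and causality is judged alike, s_c = s_p and the ratio is 1: no tilt.
- If the unequal lists lead sites to treat such events as expected after cerclage but as unrelated, hence reportable, with a pessary, then s_c > s_p and the ratio is below 1. With s_p = 0 and assumed s_c of 25%, 50% and 100%, it is 0.75, 0.50 and 0. The last is only the extreme.

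The second case is the likelier one. The trial is open label, 8.2.2 declares no known pessary risk, and section 3.4.3 says there is no evidence of more infection or other complications with it. But s_c and s_p are not in the protocol, so direction is a judgement and size is unknown.

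**5. What is lost.** Section 8.2.1 keeps the recording duty for all AEs and SAEs, and the schedule of visits makes AE collection compulsory at the baseline visit, the final visit and note review. The effect is on what is reported within 24 hours and on the SAE reports that section 8.1 gives the DMC.

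**The case against.** The strongest reply has four parts.

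- **The rule may be symmetric.** Read literally, related events are exempt in all three arms and unrelated events reportable in all three. This is right as far as it goes, and it rules out calling the tilt certain. It does not rescue the rule: a symmetric exemption of related serious events is still wrong, and the unequal lists can still influence how sites judge causality.
- **Section 2.4.2 vi makes maternal and fetal morbidity a secondary endpoint**, so infection and bleeding might be outcome events, exempt everywhere. The text does not settle this. Section 8.2.2 names only three maternal outcome events, and infection in general is not among them. The broad reading would exempt nearly every maternal serious event, which is no improvement.
- **The sentence may be a slip**, with unexpected events meant, or may only mean that unrelated events carry the label SAE while related ones are handled as SARs. Either is possible, but sites follow the text, and the exception in 8.2.3 leaves the point open. Changing that one word would also leave the expected lists unequal.
- **Nothing is lost, because everything is recorded and the DMC also sees outcomes.** The first half stands. On the DMC, the charter may give it more than SAE reports, so any harm to monitoring is an inference.

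A reader might go further and infer that cerclage harms are certainly under-counted, that reported cerclage SAEs would fall to zero, or that the DMC will be misled. The documents do not support this: some of the cerclage risks are exempt in every arm, one has no counterpart elsewhere, causality judgements are unknown, and the DMC charter is not at hand.

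**Conclusion.** Two things are established on the text. The reporting sentence in 8.2.2 leaves out treatment-related serious events and conflicts with the SAR requirement in 8.2.3. The expected risks are named unequally by arm, so reported SAE counts may not be comparable for other infection, procedural bleeding and possibly miscarriage.

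Under-reporting for cerclage is the more likely direction, on the assumption that sites judge causality in line with the lists they are given. No size can be put on it, because the protocol gives neither an SAE rate nor a share of events exempted. The weakness is confined to expedited reporting and the SAE reports the DMC receives; recorded harms data remain available for the final comparison. No sample-size or power figure is affected. The wording should be amended, since the correction is cheap and concerns safety reporting.

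**What to change.** Reconcile sections 8.2.1, 8.2.2 and 8.2.3:

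- Reword the sentence in 8.2.2 so that a serious event judged related to the allocated procedure, device or drug is not exempt from SAE reporting, and align the exception in 8.2.3 with it.
- State that the exemption for outcome events and common pregnancy events applies identically in all three arms, and say whether miscarriage and infection other than chorioamnionitis fall under it. Treatment-specific risk descriptions can stay as information but should not decide what is reported.
- Tabulate all recorded serious events, including exempt ones, by arm for the DMC and for the final harms comparison. If the DMC charter already provides this, a cross-reference is enough.

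The cost is a short amendment and a modest number of extra SAE forms. The tables draw on data that section 8.2.1 already requires sites to record.

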#### **2.4.2 Secondary endpoints**

- i) Adverse perinatal outcome, defined as a composite outcome of death (antepartum/intrapartum stillbirths plus neonatal deaths prior to discharge from neonatal services) or one (or more) of intraventricular hemorrhage,

[figure not shown]

periventricular leukomalacia, hypoxic ischemic encephalopathy, necrotizing enterocolitis, bronchopulmonary dysplasia and sepsis.

- ii) Delivery <30 & 34 completed weeks' gestation.
- iii) Gestation at delivery.
- iv) Time between intervention and delivery.
- v) Requirement for Rescue Cerclage (bulging fetal membranes).
- vi) Other maternal and fetal outcomes: clinical course, therapies administered, maternal and fetal morbidity and mortality data until discharge or 28 days post-natal (whichever soonest).
- vii) Participant and clinician's perceptions of treatment: questionnaires with a selection of participants at 0-2 weeks post procedure. Questionnaires at one year are planned if funding is obtained.
- viii) Health costs at 28 days post-natal.
- ix) Biochemical end-points (on available samples): cervical swabs will be taken to determine the presence of cervicovaginal infection and concentrations of biomarkers of preterm birth, infection and inflammation. Saliva samples will be collected for salivary hormone levels, and blood samples taken for inflammatory markers and genetic analysis. Results will be correlated with maternal and fetal outcomes.

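### Section 8.2.2 exempts outcome events from SAE status without closing the list, so with open-ended endpoint (vi) it can be read to take maternal death and life-threatening maternal events out of 24-hour reporting

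*Protocol*

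**What the plan says.** Four parts of the protocol bear on this point.

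- **Section 8.2.1** defines an adverse event as serious if, among other criteria, it "Results in death" or "Is life-threatening". Adverse events and SAEs are recorded up to 28 days after delivery.
- **Section 8.2.2** says: "Events that are primary or secondary outcome measures are not considered to be SAEs". They go on the electronic case report form instead. A maternal list follows (premature labour, premature rupture of membranes, chorioamnionitis), then an infant list of five items. Two of the infant items, perinatal death and complications of prematurity, remain reportable when unexpected. A further paragraph adds common pregnancy complications that are also not SAEs. Just before the exemption sentence, the section says that serious events unrelated to the clinical procedures are reported as SAEs.
- **Section 2.4.2, endpoint (vi)** makes "maternal and fetal morbidity and mortality data until discharge or 28 days post-natal" part of a secondary endpoint, ending at whichever of the two comes first.
- **Section 8.2.3** requires SAEs, SARs and SUSARs to reach the sponsor's trials office and the chief investigator within 24 hours, "excepting those specified in this protocol as not requiring reporting".

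**The concern.** The exemption is worded by outcome status, and endpoint (vi) has no boundary of severity, type or cause. An investigator who applies the two together can conclude that a maternal death before discharge is an outcome event, therefore not an SAE, and belongs only on the outcome form. Another investigator, reading the list as the whole exemption, would report the same death within 24 hours. Both could claim to follow the protocol.

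The classification matters because section 8.2.3 carries it through to SARs and SUSARs. An event treated as exempt does not reach the sponsor by the expedited route. The 7-day clock for a fatal or life-threatening SUSAR starts only when the sponsor becomes aware of the reaction. The event also drops out of the SAE reports that go to the DMC. Safety-reporting rules belong in the protocol, so a statistical analysis plan would not be expected to settle this.

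**Working it through.** The protocol has no figure to reproduce here. The check sets the passages side by side under each reading, then sizes the worst-case delay.

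**Literal reading**

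1. Primary and secondary outcome measures are not SAEs (8.2.2).
2. Maternal morbidity and mortality up to discharge or 28 days is a secondary outcome (2.4.2 (vi)).
3. So maternal death and life-threatening maternal morbidity in that window are not SAEs, in any arm.
4. This contradicts 8.2.1. It also conflicts with 8.2.2's own sentence on unrelated serious events: an unrelated maternal death would be both reportable and not an SAE.
5. The window is limited. SAE recording runs to 28 days after delivery, while endpoint (vi) can end earlier, at discharge. A maternal death after discharge but before day 28 stays an SAE even on this reading.

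**List reading**

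1. Only the named events are exempt. Maternal death and unlisted life-threatening events are not named, so they stay reportable.
2. Qualifiers for unexpected cases: 2 of 5 infant items carry one; 0 of 3 maternal items do.
3. Chorioamnionitis is therefore exempt with no limit of severity or unexpectedness. If it becomes life-threatening to the mother, the list points one way and 8.2.1 the other. Section 3.4.1 names infection among the risks of cerclage, so this is an event on which the arms could differ.

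**Does the text choose between them?**

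- For the list reading: the exemption sentence runs straight into the list; the next paragraph opens as an addition to it; and the qualifiers on two infant items show that outcome status alone does not always exempt.
- Against: nowhere is the list said to be complete. Membrane rupture, chorioamnionitis and low birth weight are not named in section 2.4, so they can be outcome measures only through endpoint (vi). The list thus itself treats (vi) as a source of exempt events. Rescue cerclage is a named endpoint (v) but is not listed.

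The text does not settle the question.

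**Worst-case delay to the DMC**

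- Inputs: 540 women over 36 months (section on expected duration); DMC review at least annually, first meeting at 3 months (7.14).
- Recruitment rate, assuming it is uniform: 540 / 36 = 15 women per month.
- Women randomised between reviews 12 months apart: 15 × 12 = 180.
- Women randomised by the first DMC meeting: 15 × 3 = 45.

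The 180 is an upper bound at the planned rate, not an expected value.

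**The case against.** The strongest answer is that the literal reading defeats the section it sits in. Endpoint (vi) reads like a data-collection heading. If everything under it were exempt, almost no serious maternal event before discharge could be an SAE, both lists in 8.2.2 would be redundant, and the 24-hour rule would have little left to act on. The list reading avoids this, and section 8.2.3 excepts only events that the protocol specifies. Maternal death is specified nowhere in 8.2.2.

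That argument carries weight and makes the list reading the more sensible one. It does not make it the stated one, and it leaves the unqualified maternal items untouched. The sentence on unrelated events helps only for those events; it gives no assurance for serious events that are related to treatment. The instruction in 8.2.1 to record an event when in doubt concerns recording, not 24-hour reporting.

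Two stronger inferences are tempting and should be resisted. A reader might conclude that outcome events are never SAEs, or that maternal death is plainly exempt in every arm. The qualifiers on perinatal death and complications of prematurity, the sentence on unrelated events and the end of the endpoint (vi) window all rule that out. A reader might also take 12 months and 180 women as the likely delay. The protocol does not support that: the DMC reviews outcomes as well as SAE reports (8.1), first meets at 3 months and sets its own frequency. Adverse events are also captured at the compulsory baseline and final visits, not only at note review.

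**Conclusion.** The point holds as a contradiction and an ambiguity in the reporting rule. Sections 2.4.2, 8.2.1, 8.2.2 and 8.2.3 cannot all be applied as written to a maternal death or life-threatening maternal event before discharge. Under one available reading such an event leaves 24-hour reporting; under the other it stays in, but chorioamnionitis and the other two maternal items remain exempt without limit.

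The rule applies to all 540 planned women. That is the number covered, not a number of expected events, because the protocol gives no maternal event rate. The 12-month, 180-woman gap is a worst case that assumes uniform recruitment, annual DMC meetings only, and no earlier sight of the event in outcome data. The conclusion does not depend on it: whether a maternal death is reported within 24 hours should not turn on how a site reads the list.

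**What to change.** Reconcile sections 2.4.2 (vi), 8.2.1, 8.2.2 and 8.2.3 by amending 8.2.2 in three respects:

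1. State that outcome status alone exempts nothing: only events named in 8.2.2 are exempt from SAE reporting.
2. State that an event which is fatal or life-threatening to the mother is reported as an SAE even when it is also an outcome measure. Place this so that it also governs the paragraph on common pregnancy complications.
3. Give the three maternal items the unexpectedness qualifier already attached to perinatal death and complications of prematurity.

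No separate category for maternal intensive-care admission is needed for this repair. The protocol does not use one, and the life-threatening criterion in 8.2.1 already supplies the threshold.

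The cost is a few sentences in a protocol amendment and a few extra SAE forms. Endpoints, sample size and analysis are unaffected.
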